**SMOKING**				
Smoking history	x			x
Current smoking status	x	x	x	x
Number of quit attempts	x			x
Use of electronic cigarettes	x	x	x	x
Use of combustible cigarettes	x	x	x	x
Nicotine Dependence (FTND)	x	x	x	x
Carbon monoxide measurement	x	x	x	x
**PHYSICAL HEALTH**				
BMI (kg/m^2^)	x		x	x
Physical fitness (6-minute walking test)	x			x
Systolic BP (mm/hg)	x		x	x
Diastolic BP (mm/hg)	x		x	x
Lipid profile^b^	x			x
Glucose metabolism (mmol/l)	x			x
**PATIENT REPORTS**				
Symptoms of depression and anxiety (HADS)	x		x	x
Positive and negative symptoms (PANSS-6)	x	x	x	x
Substance Use (WHO-ASSIST)	x		x	x
Cannabis Questionnaire	x		x	x
Health-related self-efficacy (PAM-13)	x		x	x
Quality of life (SF-12)	x		x	x
Self-report physical activity (PA)	x		x	x
**DEMORGAPHICS**^a^				
Age, gender	x			
Education level	x			x
Marital status	x			x
Employment status	x			x
Diagnosis of SMI	x			x
Number of years receiving mental care	x			x
Medication use	x			x
**OTHER**				
Attendance at behavioural support sessions and peer support sessions	Weekly /monthly			
Adverse event reporting	Ongoing collection			

^a^Based on patient records

^b^Cholesterol: HDL, LDL, total and triglyceride (mmol/l)

### Process evaluation

A qualitative process evaluation will be conducted alongside the RCT through semistructured interviews with a selection of FACT team members and patients from the intervention condition. The main objective will be to examine the experiences with and acceptability of the intervention from the perspectives of patients and MHCPs. Furthermore, aspects of the implementation will be evaluated in this process evaluation. At an individual patient level, the aim will be to understand participants’ experiences with and responses to the different elements of the intervention, including the barriers and facilitators experienced when following the KISMET intervention programme. At the level of FACT team professionals, we will seek to understand their experiences and satisfaction with the programme as well as the barriers to and facilitators of the implementation. All interviews will be recorded, transcribed verbatim, pseudonymised, and analysed with the analysis software MAXQDA.

### Sample size

This trial is powered to detect a difference of 15% in smoking abstinence rates between the conditions over 1 year. These rates are expected to be 30% in the intervention group and 15% in the usual care group. This difference is based on the outcomes of multiple previous randomised clinical trials [50]. Based on an expected difference of 15% in smoking cessation rates between the two conditions, the number of participants per group will be *N* = 121. Furthermore, based on results from a previous similar study, we assume a fairly small intraclass correlation coefficient of 0.05. We deem an average cluster size of 10 participants per FACT team to be feasible. We applied a conservative correction factor to account for the multilevel data structure, yielding 12.7 FACT teams. This corresponds to *n* = 127 participants per arm [51]. Assuming a loss to follow-up of 20%, we aim to include a total of 318 participants.

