**Methods:**

A pragmatic, cluster-randomised controlled trial with embedded process evaluation will be conducted. Randomisation will be performed at the level of FACT teams, which will be assigned to the KISMET intervention or a control group (care as usual). The intervention will include pharmacological treatment combined with behavioural counselling and peer support provided by trained mental health care professionals. The intervention was developed using a Delphi study, through which a consensus was reached on the core elements of the intervention. We aim to include a total of 318 people with SMI (aged 18–65 years) who smoke and desire to quit smoking. The primary outcome is smoking status, as verified by carbon monoxide measurements and self-report. The secondary outcomes are depression and anxiety, psychotic symptoms, physical fitness, cardiovascular risks, substance use, quality of life, and health-related self-efficacy at 12 months. Alongside the trial, a qualitative process evaluation will be conducted to evaluate the barriers to and facilitators of its implementation as well as the satisfaction and experiences of both patients and mental health care professionals.

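### The sample size allows for clustering with a factor of about 1.05, where its own ICC and team size give 1.45, so 318 participants provide roughly 64–70% power

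*Protocol article*

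**What the plan says.** All the figures are in the Sample size section of the protocol article.

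- Target: "This trial is powered to detect a difference of 15% in smoking abstinence rates between the conditions over 1 year".
- Rates: "These rates are expected to be 30% in the intervention group and 15% in the usual care group".
- Size before clustering: "the number of participants per group will be *N* = 121".
- Clustering inputs: "we assume a fairly small intraclass correlation coefficient of 0.05", and "We deem an average cluster size of 10 participants per FACT team to be feasible".
- Correction: "We applied a conservative correction factor to account for the multilevel data structure, yielding 12.7 FACT teams". This is equated with 127 participants per arm, with a citation but no formula.
- Final size: "Assuming a loss to follow-up of 20%, we aim to include a total of 318 participants". The abstract repeats the total: "We aim to include a total of 318 people with SMI".

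Significance level, sidedness and power are not stated. The Randomisation section makes the FACT team the unit of allocation, and the Statistical analysis section fits a random intercept for team.

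**The concern.** An ICC of 0.05 with 10 participants per team should raise the required number by nearly half. The plan raises it by 5%. The three printed figures (ICC 0.05, 10 per team, 127 per arm after starting from 121) do not fit together under the standard design effect.

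The power claim for the primary outcome is at stake. The analysis will bear the cost of clustering through its team-level random intercept, but the sample size hardly allows for it. A true 15-point effect would be missed about one time in three instead of one time in five. Calling the correction conservative tells readers that there is a margin where there is a shortfall.

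**Working it through.** **Inputs.** From the Sample size section: p1 = 0.30, p2 = 0.15, ICC = 0.05, m = 10 per team, loss 20%, and the printed results 121, 12.7, 127 and 318. Assumed because not stated: two-sided 5% and 80% power.

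**1. Reproducing the plan's own figures.**

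Pooled-variance formula for two proportions, mean rate 0.225:

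n = [1.96 × √(2 × 0.225 × 0.775) + 0.8416 × √(0.15 × 0.85 + 0.30 × 0.70)]² / 0.15² = (1.157 + 0.489)² / 0.0225 = 120.5, rounded up to 121. This matches.

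Alternatives do not give 121: one-sided 95, 90% power 161, continuity-corrected 134, unpooled 118, arcsine 119. The assumed 5% and 80% are therefore well supported.

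- 121 × 1.05 = 127.05 per arm, and 127.05 / 10 = 12.7 teams. Both match.
- 2 × 127 / 0.80 = 317.5, rounded up to 318. This matches.

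The whole chain is reproduced with a clustering factor of 1.05 = 1 + ICC. The team size enters only when participants are converted to teams.

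**2. The design effect from the stated inputs.**

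DE = 1 + (m − 1) × ICC = 1 + 9 × 0.05 = 1.45

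121 × 1.45 = 175.45, so 176 analysed per arm, or 17.6 teams of 10. Allowing for loss, 176 / 0.80 = 220 per arm, or 440 in total. (Without rounding per arm, 2 × 175.45 / 0.80 = 438.6.)

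If 10 is the number recruited and 8 are analysed, DE = 1 + 7 × 0.05 = 1.35. Then 121 × 1.35 = 163.4, so 164 analysed per arm, 205 recruited per arm and 410 in total.

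**3. What would make 127 right.** At m = 10, solving 1 + 9 × ICC = 127/121 gives ICC = 0.0055, one ninth of the stated value. At ICC 0.05, it needs about 2 participants per team.

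**4. Power of the planned trial.** Effective n per arm is n / DE, for 30% versus 15% at two-sided 5%.

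| Case | DE | Effective n per arm | Power |
|---|---|---|---|
| 127 analysed, no clustering | 1.00 | 127 | 82% |
| 127 analysed, 10 per team | 1.45 | 87.6 | 66% (64% with t on 2 × 12.7 − 2 df) |
| 127 analysed, 8 per team | 1.35 | 94.1 | 70% (68% with t on 2 × 15.9 − 2 df) |
| 159 analysed (no loss), 10 per team | 1.45 | 109.7 | 76% |

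Two sensitivity checks, both for 127 analysed per arm and a mean of 10 per team:

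- Unequal team sizes, with an assumed coefficient of variation of 0.5: DE = 1 + (1.25 × 10 − 1) × 0.05 = 1.575, and power is 63%.
- ICC of 0.01, 0.02, 0.05 and 0.10: power is 79%, 75%, 66% and 55%.

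**5. Detectable difference.** With 80% power and 15% in usual care, the intervention rate would have to be 33.0% (DE 1.45) or 32.2% (DE 1.35). The difference is 17–18 points.

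**The case against.** Three points deserve weight.

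- **The factor is inferred.** The article prints no formula, and the cited source is not available here. That 1 + ICC was used is a back-calculation, although it matches both 127 and 12.7. The finding does not depend on it: any factor that turns 121 into 127 is far below 1.45, and the section gives no reason for a smaller one.
- **The 80% benchmark is inferred too.** The plan says only that the trial is powered. The firm statement is that 127 does not preserve whatever power 121 would give without clustering. The gap between 1.05 and 1.45 needs no assumption about alpha or power.
- **The planned model may be more efficient than a single 12-month comparison.** The overall model averages over follow-up, and adjustment for prognostic variables is planned to gain precision. As an illustration, assume three follow-ups, a constant 15-point effect, a team effect that persists over time and a within-patient correlation ρ. The variance factor is then (1 + 2ρ)/3 + 0.45. For ρ of 0.4, 0.6 and 0.8 this is 1.05, 1.18 and 1.32, with power of about 80%, 75% and 71%. So 64–70% describes the 12-month comparison and not necessarily the mixed model. This does not repair the section. It claims no such gain, it presents the factor purely as a multilevel correction, and the Primary outcome section places the outcome at 12 months.

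It is also fair to say that the defect costs power only. The team-level random intercept keeps clustering in the analysis, and the confidence interval will show the imprecision.

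**Conclusion.** The concern holds. On the plan's own ICC and team size, 127 per arm is too few and the correction is the reverse of conservative. For a comparison of 30% with 15% at 12 months, 318 recruited with 20% loss gives about 66% power, or 64–70% across the normal and t calculations with 10 or 8 analysed per team. The stated inputs require about 440 recruited (410 if 10 recruited means 8 analysed), so the target is short by 440 − 318 = 122 (or 92). Even with no loss to follow-up, power is 76% with 10 per team.

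This rests on two-sided 5% and 80% power, inferred from N = 121, and on no credit for repeated measures or covariates, since the section takes none.

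**What to change.** Rewrite the clustering step in the Sample size section:

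1. State alpha, sidedness, power and the formula DE = 1 + (m − 1) × ICC = 1.45, and say whether 10 per team means recruited or analysed.
2. Then choose one of two courses. Raise the target to 176 analysed per arm, about 440 recruited. Or, if 318 is the feasible number, keep it and state that it gives about 66% power for 15% versus 30% and detects about 18 points with 80% power.
3. Delete the word conservative.
4. If the smaller factor was meant to reflect gains from repeated measures or covariate adjustment, say so and give the assumed correlations.

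Giving a whole number of teams per arm, and power over ICC 0.01–0.10 (79% down to 55%), would help but is good practice rather than correction.

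Keeping 318 means a wording change and a less favourable power figure, with no extra patients. Raising the target means about 122 more participants and more teams, which matters because the Discussion already expects recruiting teams and patients to be difficult. The total in the abstract changes only in that case.

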### Statistical analysis

The characteristics of people with SMI in the intervention and control groups will first be presented at baseline and using descriptive statistics (mean [standard deviation], median [range], or frequencies [percentage]). All analyses will be conducted on an intention-to-treat basis, including all randomised patients in the groups to which they were allocated where data are available.

To compare the effects of the intervention with those of usual care on CO-verified smoking cessation (primary outcome) between baseline and 3, 6, and 12 months, a mixed model with a three-level structure (observations clustered within patients, patients clustered within FACT teams, and FACT teams clustered within institutions) will be used, including a random intercept the patient, FACT team, and institution levels [52]. The necessity of random slopes will be assessed using the likelihood ratio test, which will compare the model with random intercepts with a model with random intercepts and random slopes.

The first model will be an ‘overall’ model, with only the treatment variable included. This will provide information about the treatment effect of the primary outcome (odds ratio, 95% confidence interval, and *p*-value), which can be interpreted as the average overall treatment effect over time. Subsequent analyses will include a categorical variable for time (as a dummy variable) as well as an interaction between treatment and time to enable an in-depth investigation of the intervention’s effects at different time points [52].

For binary secondary outcome variables, a similar analysis strategy to the one above will be used. For continuous variables, we will run the first model as mentioned as well as use a longitudinal analysis of covariance to appropriately adjust for the baseline value of the outcome variable [53].

All of the aforementioned models will be additionally adjusted for prognostic variables to increase the precision of the crude treatment effects [54]. These prognostic variables will be identified through a literature study and directed acyclic graphs (DAGs) [55].

Finally, a descriptive analysis will be performed to compare the number of cigarettes smoked per day over time between the two groups as well as attendance at group sessions within the intervention group.

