### Participants

Participants will be people with SMI who receive treatment from FACT teams. Patients who fulfil the following criteria will be eligible for inclusion:Fulfils the criteria of SMI according to Delespaul and the SMI Consensus Group, which are defined as follows [34]: presenting a non-transient (structural or long-term for several years) psychiatric disorder, for which coordinated care from a care network is necessary and which is not in symptomatic remission; presenting severely impaired social and/or occupational functioning which is not in functional remission;Aged ≥18 years;Current smoker (≥ 5 cigarettes) without a quit attempt in the past month;Expresses an interest in stopping / cutting down smoking;Willing and able to sign informed consent.

Patients who are pregnant or breastfeeding, have severe cognitive impairments, present a primary diagnosis of substance use disorder (with the exception of cannabis use disorder), or are experiencing an acute psychiatric crisis or acute physical disease at the time of inclusion will not be eligible to participate.

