### Main outcome measures

#### Primary outcome

##### Smoking

The primary outcome parameter is smoking behaviour at 12 months. This outcome is defined by exhaled carbon monoxide (CO) measured with a CO monitor and self-report. We define smoking cessation as a CO reading of less than 10 ppm (ppm).

Smoking history and current smoking status will be assessed through a short questionnaire.

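### The primary outcome is set at 12 months, but the odds ratio and p-value tied to it come from a model that averages the treatment effect over visits

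*Protocol article*

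**What the plan says.** The outcome section of the protocol article states: "The primary outcome parameter is smoking behaviour at 12 months". Cessation is defined there by exhaled carbon monoxide below 10 ppm, together with self-report.

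The Statistical analysis section describes a mixed model for the effect "on CO-verified smoking cessation (primary outcome) between baseline and 3, 6, and 12 months". It then sets out two steps:

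- **Step 1.** "The first model will be an ‘overall’ model, with only the treatment variable included". Of this model the article says: "This will provide information about the treatment effect of the primary outcome", and it lists the odds ratio, 95% confidence interval and p-value as the output. The result is one "which can be interpreted as the average overall treatment effect over time".
- **Step 2.** Subsequent analyses add time as a categorical variable and its interaction with treatment, to look at effects at the separate time points.

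The Sample size section rests on a single pair of abstinence rates, 30% against 15%, over one year. No section says that the 12-month contrast from step 2 is the decisive one.

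**The concern.** The endpoint and the analysis name different quantities. The endpoint is a state at one visit. The step 1 model estimates one treatment effect common to all modelled visits. The two agree only if the effect is the same at 3, 6 and 12 months.

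A constant effect cannot be taken for granted. The description of behavioural counselling treats lapse and relapse as events that can occur during quitting. If abstinence gained early is later lost, the averaged effect credits it although nothing remains at 12 months. If the effect builds up slowly, the averaged effect understates it. In either case the trial could report one p-value for the primary outcome from step 1 and a discordant 12-month p-value from step 2, with no stated rule for which one answers the primary question.

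**Working it through.** **1. The plan's own figure.** Two proportions, 0.30 and 0.15, pooled variance, no continuity correction. Two-sided α = 0.05 and 80% power are inferred, because the article states neither and they return its figure:

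n = [1.96·√(2·0.225·0.775) + 0.8416·√(0.30·0.70 + 0.15·0.85)]² / 0.15² = 120.5, so 121 per group. This matches the article. The sizing is for one comparison of two proportions, not for an effect averaged over visits.

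**2. Inputs for the check.**

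- From the Sample size section: 127 per arm; ICC 0.05 and 10 patients per team, giving a design effect of 1 + 9 × 0.05 = 1.45.
- Assumed, not in the document: the abstinence rate at each visit, and an exchangeable within-patient correlation ρ of 0.4, 0.6 or 0.8.

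**3. Formula.** In each arm, the variance of a patient's mean over three visits is V = (1/9)·[Σ sⱼ² + 2ρ·Σ sⱼsₖ], with sⱼ = √(pⱼ(1 − pⱼ)). The standard error of the averaged difference is √[(V₁ + V₀)·1.45/127], and the probability of significance is P(|Z| > 1.96). This is a risk-difference approximation to the planned logistic mixed model.

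**4. Early effect that fades to nothing.** Intervention 35/28/15%, control 20/17/15%. The differences are 15, 11 and 0 points, so the averaged difference is 26/3 = 8.67 points.

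| ρ | V₁ | V₀ | SE | Z | P(significant) |
|---|---|---|---|---|---|
| 0.4 | 0.1103 | 0.0856 | 0.0473 | 1.83 | 45% |
| 0.6 | 0.1345 | 0.1046 | 0.0522 | 1.66 | 38% |
| 0.8 | 0.1587 | 0.1236 | 0.0568 | 1.53 | 33% |

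A 12-month test would be significant in 5% of such trials.

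**5. Effect that builds up.** Intervention 20/25/30%, control 15% throughout. The averaged difference is (5 + 10 + 15)/3 = 10 points. P(significant) is 58%, 50% and 44% for ρ = 0.4, 0.6 and 0.8. For the 12-month comparison alone, SE = √[(0.21 + 0.1275)·1.45/127] = 0.0621 and Z = 0.15/0.0621 = 2.42, so power is about 68%.

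**6. Constant effect.** 30% against 15% at every visit. The averaged test has power of 88%, 81% and 74% for ρ = 0.4, 0.6 and 0.8; the 12-month test again has about 68%.

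**7. Simulation with the mixed model itself.** 16 teams per arm, 8 patients per team, control abstinence 15% at each visit, latent team correlation 0.05 and latent within-patient correlation 0.6 (both assumed), no institution effect, 1,000 replicates. The treatment-only logistic mixed model over 3, 6 and 12 months was compared with a t-test on team means at 12 months.

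| Intervention rates at 3/6/12 months | Treatment-only model | 12-month test |
|---|---|---|
| 15/15/15% (null) | 5% | 4% |
| 30/30/15% | 65% | 6% |
| 35/25/15% | 65% | 5% |
| 30/22.5/15% | 47% | 5% |
| 15/15/30% | 28% | 73% |
| 30/30/30% | 90% | 73% |

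The pattern is the same as in steps 4 to 6. The two columns also differ in estimator, so part of each gap is not due to the estimand.

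**The case against.** **No confirmatory rule is stated.** The article calls the averaged model the first one and says that it gives information about the effect. It sets no success criterion, and the treatment-by-time model, which yields the 12-month contrast, is prespecified in the same paragraph. A fuller analysis plan could say which contrast decides. This stands as a limit: a reader might infer that the trial will be declared successful on early quitting alone, and the article does not say so. It does not remove the mismatch, because the text attaches the primary-outcome odds ratio and p-value to the averaged model.

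**The mismatch could be resolved the other way.** The sample size refers to rates over one year, and the abstract gives smoking status as the primary outcome without tying 12 months to it unambiguously. Redefining the primary outcome as average abstinence over follow-up would also be coherent. That stands, but the outcome section as written says 12 months.

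**The visit profiles are invented.** This is correct; the document gives only one pair of rates. The percentages are illustrations.

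Three stronger readings are tempting and are not supported:

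- *Baseline rows dilute the effect.* The wording "between baseline and 3, 6, and 12 months" may only describe the period of comparison. If baseline were modelled and every patient counted as smoking, 30% against 15% would become 22.5% against 11.25%, but the odds ratio would move only from 2.43 to 2.29, about 7% on the log scale. In simulation (200 replicates) rejection rates did not change. Nor are zero events at baseline guaranteed: entry requires "Current smoker (≥ 5 cigarettes) without a quit attempt in the past month" with no carbon monoxide threshold.
- *The patient-specific odds ratio is an error.* It is a standard property of a logistic model with a patient random intercept, and the article does not claim a population-averaged one.
- *Effects on continuous outcomes are halved.* That needs baseline to be modelled as an outcome, which is not stated, and a longitudinal analysis of covariance is already planned.

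**Conclusion.** The concern holds as a mismatch between the endpoint and the analysis tied to it. The declared endpoint is at 12 months, the primary-outcome p-value belongs to an effect averaged over visits, and nothing gives the 12-month contrast precedence.

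The averaged test is significant in about 33–45% of trials with no 12-month effect under the fading profile of step 4. It has 44–58% power, against about 68% for the 12-month test, when the effect grows from 5 to 15 points. These sizes rest on assumed visit rates and correlations, with 127 per arm and a design effect of 1.45. The direction needs only that the effect changes over time. The 12-month effect is not missing from the plan: it can be estimated from the later model, but it is not named as the primary test.

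**What to change.** State in the Statistical analysis section that the single primary test is the 12-month treatment contrast from the treatment-by-time mixed model already planned, with 3, 6 and 12 months as outcome visits and baseline not modelled as an outcome. Report its odds ratio, 95% confidence interval and p-value as the primary result, and list the time-averaged odds ratio as secondary. Settle this before any comparison by arm is seen. If the investigators do want the average over follow-up, the alternative is to redefine the primary outcome that way and justify it.

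The change takes a few sentences and no new data. The real cost is power if the effect is constant over time: about 68% for the 12-month contrast against 74–88% for the average, under the assumptions above. A marginal 12-month risk difference with its 95% confidence interval, beside the odds ratio, would help readers relate the result to the 15-point difference used for sizing. It is an optional aid to interpretation and corrects no error.

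### The primary odds ratio is patient-specific, while the trial is planned on population abstinence rates; label it as such and report a population-averaged difference with it

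*Protocol article*

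**What the plan says.** The Statistical analysis section of the protocol article fits a mixed model to CO-verified cessation at 3, 6 and 12 months, "including a random intercept the patient, FACT team, and institution levels". The first model contains only treatment. Its result is an odds ratio with 95% confidence interval and p-value, "which can be interpreted as the average overall treatment effect over time". Later models add time and a treatment-by-time interaction, to look at individual time points. No other measure of the treatment effect is named for the primary outcome.

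The Sample size section works on a different scale: "This trial is powered to detect a difference of 15% in smoking abstinence rates between the conditions over 1 year". It continues: "These rates are expected to be 30% in the intervention group and 15% in the usual care group". The only correlation given is in the same section, "we assume a fairly small intraclass correlation coefficient of 0.05", followed directly by the team size: "We deem an average cluster size of 10 participants per FACT team to be feasible".

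**The concern.** In a logistic model with a patient random intercept, the treatment coefficient compares two patients who share the same random effect. It is not the log odds ratio obtained by comparing abstinence proportions between the arms. The two differ whenever the random-intercept variance is above zero, and the gap grows with that variance. Repeated abstinence readings in one person can be expected to be correlated, so the patient variance may well be large.

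The planning figures are population proportions. The single effect measure named for the primary outcome therefore cannot be set directly against the 15-point difference that the trial was sized to detect, or against trials that report abstinence by arm. The treatment-by-time odds ratios are conditional in the same way, so moving to the 12-month contrast does not remove the mismatch. At stake is how the headline effect size is read. The p-value is not affected.

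**Working it through.** **1. Confirm that the planning contrast is marginal.** The inputs are 30% and 15% (Sample size). Alpha and power are not stated, so I assume two-sided 0.05 and 80%. The two-proportion formula with pooled variance and no continuity correction is

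n = [1.960 × √(2 × 0.225 × 0.775) + 0.842 × √(0.30 × 0.70 + 0.15 × 0.85)]² / 0.15²

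= [1.960 × 0.5906 + 0.842 × 0.5809]² / 0.0225 ≈ 2.711 / 0.0225 ≈ 120.5, which rounds up to 121.

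This matches the article: "the number of participants per group will be *N* = 121". The plan is therefore built on two population proportions. The corresponding marginal odds ratio is (0.30/0.70) / (0.15/0.85) = 2.43.

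**2. Find the conditional odds ratio that the same rates imply.** Let the patient intercept be normal with standard deviation σ. For each σ, solve numerically for the intercept η in each arm such that the average of expit(η + σZ) over a standard normal Z equals 0.15 (usual care) or 0.30 (intervention). The conditional odds ratio is exp(η₁ − η₀). This takes the rates as equal at all visits and puts all the random variation in one normal intercept.

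The article gives neither σ nor a within-patient correlation, so I use an assumed range. The correlation below is between two abstinence readings in the same patient, averaged over the two arms.

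| Assumed correlation | σ | η₀ (15%) | η₁ (30%) | Conditional OR | Ratio to 2.43 |
|---|---|---|---|---|---|
| 0.3 | 1.75 | −2.556 | −1.283 | 3.57 | 1.47 |
| 0.4 | 2.29 | −2.990 | −1.507 | 4.41 | 1.82 |
| 0.5 | 2.99 | −3.602 | −1.818 | 5.95 | 2.45 |
| 0.6 | 3.97 | −4.512 | −2.281 | 9.31 | 3.83 |

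On the log-odds scale, where the model works, the ratios are about 1.4, 1.7, 2.0 and 2.5. The usual attenuation approximation √(1 + 0.346σ²) gives 1.44, 1.68, 2.02 and 2.54, in agreement.

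**3. Sensitivity to the unknown variance.** With variance = ICC/(1 − ICC) × π²/3 on the latent scale, the conditional odds ratio is 2.49 (1.03 times the marginal) at ICC 0.05, 3.65 (1.50 times) at 0.50, 5.40 (2.23 times) at 0.70 and 18.8 (7.75 times) at 0.90. The article's 0.05 is given with the team cluster size and concerns patients in the same team. It says nothing about repeated readings in one patient, so the 1.03 figure is no guide to the gap here.

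**4. What a misreading would look like.** If a conditional odds ratio of 5.95 were applied to a 15% control rate, the odds would be 5.95 × 0.15/0.85 = 1.05 and the implied abstinence 1.05/2.05 = 51%. The true figure in this example is 30%.

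**The case against.** The strongest reply is that the plan says nothing false. The sentence contrasts a treatment-only model with later models by time point, so the average is over visits, not over patients. A conditional odds ratio is a legitimate target, the test is valid, and a trial may be sized on a difference in proportions and analysed with a logistic model. Nothing in the article proposes converting the odds ratio to a percentage as in step 4, and nothing rules out tables of abstinence by arm. A condensed article may also leave post-estimation output to the full analysis plan.

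Most of this stands. A reader might infer that the plan claims a population-averaged effect; the wording does not expressly do so and is ambiguous rather than plainly wrong. A reader might also infer that the analysis overstates the planned effect by a fixed factor. The documents do not support that either: any factor depends on a patient variance they do not give, and overstatement arises only if the odds ratio is read as a population effect.

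What remains does not rest on an omission. The article itself names the model, the effect measure and its interpretation. As described, that measure is on a different scale from the article's own planning target, and the word average invites a reader to overlook this.

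**Conclusion.** The point holds as a cheap improvement and is not a must-fix. The primary odds ratio is conditional on the patient's random effect, and its description does not say so. It is not the quantity behind 30% v 15%. If the planned rates held at every visit, it would be about 1.5 to 4 times the marginal value of 2.43, given an assumed within-patient correlation of 0.3 to 0.6 and normal random intercepts. A lower or higher correlation would give a smaller or larger gap. Neither the validity of the test nor the sample size is in question on this point.

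**What to change.** Keep the mixed model for the test. In the Statistical analysis section, describe its odds ratio as patient-specific (conditional on the random effects) and say that the averaging meant is over follow-up visits. Report with it the population-averaged difference in CO-verified abstinence with 95% confidence interval, plus a marginal odds ratio or risk ratio, both overall and at 12 months. These come from averaging the predicted risks over the random effects after fitting the model. Because the patient variance may be large, check that the estimates are stable when the number of integration points is increased.

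The cost is a few words in the plan and one post-estimation step, with no new data and no change to design. The marginal ratio will be smaller and less striking than the model's odds ratio, but it can be compared with the planned difference.
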